### Informed consent and randomization

Those who agree to participate in the study will have a computer connected to the internet, and each participant will complete the informed consent form online and register in the program by creating a personal username and password. All participants will complete an initial short sociodemographic and clinical questionnaire (see details in the measures section). To ensure concealment of allocation, the APOLO-Bari system will then automatically randomize (computer-generating random numbers) the participants on a 1:1 basis, matching for age, sex, and surgery type.

After randomization, intervention group members will receive full access to the three components of the APOLO-Bari program in their personal accounts. The intervention will last for 12 months, and a 6-month period will follow, with no program access possible. During the intervention period, the system will record data on log-in frequency, task submission, and weekly monitoring from the intervention group.

The control group will only have access to general information on obesity and bariatric surgery and to the set of self-report measures at the different assessment times. The control group participants will be informed of the assessment times and the possibility of accessing the full program after the study is complete. Both groups will receive reminder emails every time a questionnaire or activity is available.

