### Psychological self-report measures

Repetitive Eating Questionnaire [12]: This self-report questionnaire assesses a grazing-type eating pattern through 15 items, resulting in two subscales that reflect compulsive grazing and non-compulsive grazing subtypes.

Depression Anxiety Stress Scales [36]: This 21-item questionnaire generates subscales on depression, anxiety, and stress.

Eating Disorder – 15 [37]: This 15-item questionnaire assesses eating disorder cognition and behaviors, with subscales for weight and shape concerns and for eating concerns.

Negative Urgency Subscale [38]: This 12-item scale assesses an individual’s tendency to surrender to strong impulses, particularly when accompanied by negative emotions, such as depression, anxiety, or anger.

Influence of weight: Developed by the research team, this 12-item measure inquires about the influence of weight in different areas of life (e.g., intimate relationships, professional roles, self-esteem).

Satisfaction questionnaire: Developed by the research team, this 19-item questionnaire addresses the utility and feasibility of the program from the patient’s perspective.

All questionnaires have been used with this sample by the research team in previous studies, and show good internal consistency for use with bariatric surgery patients.

Table 3 presents a summary of the self-report measures used for each group at each assessment time.

**Table 3 Tab3:** Timeline for the self-report measures

	Registration	Baseline (*T* _b_)	4-month midterm assessment (*T* _m4_)	8-month midterm assessment (*T* _m8_)	Final (end of treatment) assessment (*T* _f_)	6-month follow-up assessment (*T* _fu6_)	12-month follow-up assessment (*T* _fu12_)	Weekly
Sociodemographic weight history	X	–	–	–	–	–	–	–
Clinical inventory	–	X	X	X	X	X	X	–
Repetitive Eating Questionnaire [12]	–	X	X	X	X	X	X	–
Depression Anxiety Stress Scales [36]	–	X	X	X	X	X	X	–
Eating Disorder – 15 [37]	–	X	X	X	X	X	X	–
Negative Urgency Subscale [38]	–	X	X	X	X	X	X	–
Influence of weight	–	X	X	X	X	X	X	–
Satisfaction questionnaire	–	–	–	–	Intervention group	–	–	–
Eating and exercise behaviors (Table 4)	–	Control group	Control group	Control group	Control group	X	X	Intervention group

*X* available for both intervention and control group

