### Weekly assessment

The weekly assessment includes three questions that will provide information for the feedback message and six other questions designed to monitor the relevant behaviors for this population. For the feedback message, the participants respond to the number of days in the previous week that they engaged in grazing, binge eating, or overeating. Definitions are provided based on the definitions proposed by Conceição et al. [12] for grazing, and by Fairburn et al. [39] for overeating eating and binge eating episodes. Other questions involve additional eating behaviors (e.g., skipping meals, the level of control over eating) and active or sedentary behaviors. Table 4 presents a list of the items used in the weekly assessment.

**Table 4 Tab4:** Weekly assessment questionnaire for the feedback messaging system

Please respond to the following questions by referring to the previous week (7 days). During the past week…
1. How many days did you skip meals (for example, breakfast, morning snack, lunch)?
2. How many days did you graze or nibble on small or modest amounts of food throughout the day in a repetitive and unplanned manner?
3. How many days did you feel that you overate (for example, had a second helping, continued eating after satiation, overate without feeling hungry)?
4. How many days did you feel that you overate or could not resist eating because you were feeling anxious, nervous, or sad, or other emotions?
5. How many days did you feel that you lost control over what you were eating (for example, being unable to resist eating or to stop eating after you started)
a. On a scale from 1 to 5 (with 1 indicating very low and 5 indicating an extreme loss of control), to what extent did you feel a sense of loss of control during those situations?
6. How many days did you eat compulsively, losing control while eating an amount of food that was extremely large given the situation (for example, twice or more than what others would eat under the same situation)?
a. On a scale from 1 to 5 (with 1 representing very low and 5 representing an extreme loss of control), to what extent did you feel a sense of loss of control during those situations?
7. How many days did you walk for more than 15 minutes?
8. How many days were you involved in structured physical activity for more than 30 minutes, such as going to the gym, playing soccer, or swimming?

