9. On average, how many hours per day did you spend sitting for any reason (for example, working, browsing the internet, driving, watching TV on the sofa)?
10. Did you have surgery to remove the extra hanging skin this week? Yes, Date__; No.

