### Primary and secondary outcome measures

The primary outcome measure will be weight regain assessed at baseline (*T*_b_), end of treatment (*T*_f_), and follow-up (*T*_fu6_ and *T*_fu12_). Other weight outcome measures, such as variance in weight loss estimations, will be tested. The following formulas will be used to compute these outcomes [40]:

$$ \mathrm{Percentage}\ \mathrm{of}\ \mathrm{total}\ \mathrm{weight}\ \mathrm{regain} = \left(\frac{\mathrm{current}\ \mathrm{weight}-\mathrm{nadir}\ \mathrm{weight}}{\mathrm{weight}\ \mathrm{presurgery} - \mathrm{nadir}\ \mathrm{weight}}\right)\times 100; $$

$$ \mathrm{Percentage}\ \mathrm{of}\ \mathrm{excessive}\ \mathrm{weight}\ \mathrm{regain}=\left(\frac{\mathrm{current}\ \mathrm{weight} - \mathrm{nadir}\ \mathrm{weight}}{\mathrm{excess}\ \mathrm{weight}}\right)\times 100; $$

$$ \mathrm{Percentage}\ \mathrm{of}\ \mathrm{total}\ \mathrm{weight}\ \mathrm{loss}=\left(\frac{\mathrm{weight}\ \mathrm{presurgery} - \mathrm{current}\ \mathrm{weight}}{\mathrm{weight}\ \mathrm{presurgery}}\right)\times 100; $$

$$ \mathrm{Percentage}\ \mathrm{of}\ \mathrm{excessive}\ \mathrm{weight}\ \mathrm{loss}=\left(\frac{\mathrm{weight}\ \mathrm{presurgery} - \mathrm{current}\ \mathrm{weight}}{\mathrm{excess}\ \mathrm{weight}}\right)\times 100; $$

$$ \mathrm{Percentage}\ \mathrm{of}\ \mathrm{alterable}\ \mathrm{weight}\ \mathrm{loss}=\left(\frac{\mathrm{body}\ \mathrm{mass}\ \mathrm{index}\ \mathrm{presurgery} - \mathrm{current}\ \mathrm{body}\ \mathrm{mass}\ \mathrm{index}}{\mathrm{body}\ \mathrm{mass}\ \mathrm{index}\ \mathrm{presurgery} - 13}\right)\times 100\ . $$

Excess weight will be calculated based on metropolitan guidelines [41].

Secondary outcome measures will include behavioral and psychological outcome measures: the number of days engaging in maladaptive eating behaviors (such as grazing, binge eating, or overeating episodes) as well as the number of hours of sedentary and physical activities in the previous month. Psychological symptoms assessed with self-report measures will also be tested. Differences between the intervention group and the control group will be tested at all assessment times. Additionally, midterm secondary outcomes will be tested as predictors of weight outcomes in later assessments.

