Baseline (*T*_b_), midterm (*T*_m4_ and *T*_m8_), end of treatment (*T*_f_), and follow-up (*T*_fu6_ and *T*_fu12_) data on primary and secondary outcomes will be compared between the two groups. Repeated measures gathered for the intervention group during the feedback messaging system will be used to study the effect of behavior and psychological outcomes on weight. Repeated assessment enables testing of the course of relevant factors and their relation to weight.

Moderators and nonspecific predictor variables that can affect outcomes without stemming from the intervention are assessed at baseline (*T*_b_); these variables include pre-surgery body mass index, type of surgery, sex, severity of general psychopathology, and frequency of maladaptive behaviors.

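### Table 3 gives the eating and exercise form to the two arms on different schedules until end of treatment, states no T_b value for the intervention arm, and cannot supply the activity outcome as defined

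*Protocol article*

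**What the plan says.** - **Schedule (Psychological self-report measures, Table 3).** The row "Eating and exercise behaviors (Table 4" names the control group at T_b, T_m4, T_m8 and T_f and the intervention group under the weekly column. An X, defined as "available for both intervention and control group", appears only at T_fu6 and T_fu12.
- **Instrument (Weekly assessment, Table 4).** The form opens with "Please respond to the following questions by referring to the previous week (7 days". Items 7 and 8 count days of walking or structured activity above a 15- or 30-minute threshold. Item 9 asks for average daily sitting hours. Item 10 asks "Did you have surgery to remove the extra hanging skin this week".
- **Outcomes (Primary and secondary outcome measures).** The secondary outcomes include "the number of days engaging in maladaptive eating behaviors" and the "number of hours of sedentary and physical activities in the previous month". Arm differences are to be tested at each assessment. Baseline moderators, stated as assessed at T_b, include "severity of general psychopathology, and frequency of maladaptive behaviors".
- **Sequence (Informed consent and randomization).** After a short sociodemographic and clinical questionnaire, "the APOLO-Bari system will then automatically randomize" participants. Program access for the intervention arm follows.
- **Feedback (The weekly feedback monitoring system).** Each weekly submission triggers an immediate tailored message.
- **Abstract.** Both groups are said to complete similar questionnaires at baseline and every 4 months.

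**The concern.** During treatment, the form that records eating and activity behavior is a visit questionnaire in one arm and a working part of the program in the other. A difference between arms on these items may reflect changed behavior, or changed reporting after many prompts and feedback messages. Without a T_b value on the same form in the intervention arm, change from baseline on it cannot be compared, and a T_b moderator taken from it would exist in one arm only. The hierarchical models in the Statistics section tolerate unequal numbers of observations, but they do not correct for measurement that differs by arm.

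Two further problems lie in the form itself. It does not carry the unit and window of the stated activity outcome. It also records an event that lowers weight directly, skin-removal surgery, far more completely in one arm than in the other.

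**Working it through.** The plan gives no figure to reproduce here. The check sets the schedule, the items and the outcome definitions side by side.

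**1. Is the row read correctly?** Table 3 has eight columns and this row has eight cells, so nothing suggests a shifted column.

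| Time | Control | Intervention |
|---|---|---|
| Registration | no | no |
| T_b | yes | no |
| T_m4 | yes | no |
| T_m8 | yes | no |
| T_f | yes | no |
| T_fu6, T_fu12 | yes | yes |
| Weekly | no | yes |

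Fixed assessments shared by the arms: 0 of 4 from T_b to T_f, and 2 of 2 in follow-up. Taking the 12-month intervention as 52 weeks (an assumption), there are 4 scheduled administrations in controls and about 52 in the intervention arm: 52 / 4 = 13 times as many.

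**2. Can a weekly entry serve as T_b?** The weekly tool opens after randomization, with the rest of the program. Nothing in the article designates a weekly entry as the T_b, T_m4, T_m8 or T_f value. A first weekly entry would in any case follow allocation and program access.

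**3. Can Table 4 supply the stated outcomes?**

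| Outcome as stated | Table 4 source | Derivable? |
|---|---|---|
| Days of grazing, binge eating, overeating | day counts over 7 days | yes, for 7 days |
| Sedentary hours, previous month | item 9, daily sitting hours over 7 days | for 7 days only |
| Physical activity hours, previous month | items 7 and 8, days above a threshold | no |

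For physical activity, a participant reporting 3 days a week on item 8 for four weeks has done more than 3 x 4 x 0.5 = 6 hours, with no upper bound. This holds in both arms at all times. For sitting, one form covers 7 / 28 = 25% of a four-week month.

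**4. Item 10.** With every prompt answered, the intervention arm is asked about all 52 treatment weeks. Controls have four forms up to T_f. One is at T_b, so three cover weeks after baseline, leaving 52 - 3 = 49 of 52 weeks about which they are never asked. The clinical inventory, as described, does not cover skin surgery either.

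**5. Order of T_b and allocation.** The T_b cell for this form differs by arm, so for this form the allocation must be known when it is issued. For the other T_b scales and the baseline weighing the article gives no explicit order. It puts a clinical questionnaire before randomization, while Table 3 puts the clinical inventory at T_b. The assessment flow chart is not available in the text reviewed.

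**The case against.** The strongest defense is that controls get the form at visits because the other arm already completes it weekly. The items and the 7-day recall are the same, so a weekly entry should exist at or near T_m4, T_m8 and T_f and can be matched to the control form. The article also assigns the repeated weekly data to studying behavior and weight within the intervention arm, and the monitoring is itself part of the treatment under test. Much of this stands: the post-baseline values are recoverable if the matching rule is fixed in advance. It does not supply a value from before program access, and it does not remove the effect of prompts and feedback on reporting.

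Four stronger readings are tempting but go beyond the document:

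- *The primary outcome is compromised.* Weight is measured by the research team in both arms at the same six times. Item 10 bears on how weight is interpreted, not on how it is measured.
- *The arms are compared over different recall windows.* That would need four summed intervention weeks set against one control week, or a control week scaled up. No section proposes either. The monthly window may also attach only to the hours of activity and not to the eating days.
- *Eating behavior cannot be baseline-adjusted at all.* The Repetitive Eating Questionnaire and the Eating Disorder-15 are given to both arms at T_b and cover part of it. Neither is described as giving the day counts or any measure of activity, so the gap is narrower but remains.
- *All baseline scales are answered after allocation is known.* This is an inference from one row and from an ambiguous sequence. It is a question to settle, not an established fault.

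**Conclusion.** The point holds in limited form and should be fixed. From T_b to T_f the arms share the Table 4 form at none of the four fixed assessments. The intervention arm has no stated T_b value on it, which conflicts with the planned comparisons at every assessment and with the T_b moderator, if that moderator comes from this form. Hours of physical activity cannot be derived in either arm. Controls are not asked about skin surgery in 49 of 52 treatment weeks, assuming a 52-week year.

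The consequence falls mainly on the behavioral secondary outcomes. No numerical bias is claimed, because its size depends on how reporting reacts to prompts and feedback, and the document gives no information on that. The structural findings depend only on Tables 3 and 4 as printed.

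**What to change.** 1. Give both arms the Table 4 form at T_b, before program access, and at T_m4, T_m8 and T_f. At minimum, collect it at T_b in both arms and pre-specify which weekly entry, within what window around each visit, counts as the intervention arm's T_m4, T_m8 and T_f value.
2. Base between-arm comparisons only on these 7-day values. Keep the remaining weekly data for analyses within the intervention arm.
3. Restate the outcomes as days of each eating behavior, days of walking and structured activity, and sitting hours per day, all over the previous 7 days.
4. Ask item 10 as *since the last assessment* in both arms at each visit.
5. Confirm that T_b measures are complete before allocation is revealed. If they are not, set the system to randomize only once they are.

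The cost is one short form at up to four existing assessments in the intervention arm, an amended Table 3 and outcome definition and, if step 5 requires it, a software setting. Recruitment was still open when the article was written. The change helps only participants not yet randomized as regards T_b, because a baseline that was not collected cannot be recovered.

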### Weekly assessment

The weekly assessment includes three questions that will provide information for the feedback message and six other questions designed to monitor the relevant behaviors for this population. For the feedback message, the participants respond to the number of days in the previous week that they engaged in grazing, binge eating, or overeating. Definitions are provided based on the definitions proposed by Conceição et al. [12] for grazing, and by Fairburn et al. [39] for overeating eating and binge eating episodes. Other questions involve additional eating behaviors (e.g., skipping meals, the level of control over eating) and active or sedentary behaviors. Table 4 presents a list of the items used in the weekly assessment.

**Table 4 Tab4:** Weekly assessment questionnaire for the feedback messaging system

Please respond to the following questions by referring to the previous week (7 days). During the past week…
1. How many days did you skip meals (for example, breakfast, morning snack, lunch)?
2. How many days did you graze or nibble on small or modest amounts of food throughout the day in a repetitive and unplanned manner?
3. How many days did you feel that you overate (for example, had a second helping, continued eating after satiation, overate without feeling hungry)?
4. How many days did you feel that you overate or could not resist eating because you were feeling anxious, nervous, or sad, or other emotions?
5. How many days did you feel that you lost control over what you were eating (for example, being unable to resist eating or to stop eating after you started)
a. On a scale from 1 to 5 (with 1 indicating very low and 5 indicating an extreme loss of control), to what extent did you feel a sense of loss of control during those situations?
6. How many days did you eat compulsively, losing control while eating an amount of food that was extremely large given the situation (for example, twice or more than what others would eat under the same situation)?
a. On a scale from 1 to 5 (with 1 representing very low and 5 representing an extreme loss of control), to what extent did you feel a sense of loss of control during those situations?
7. How many days did you walk for more than 15 minutes?
8. How many days were you involved in structured physical activity for more than 30 minutes, such as going to the gym, playing soccer, or swimming?
9. On average, how many hours per day did you spend sitting for any reason (for example, working, browsing the internet, driving, watching TV on the sofa)?
10. Did you have surgery to remove the extra hanging skin this week? Yes, Date__; No.

### Primary and secondary outcome measures

The primary outcome measure will be weight regain assessed at baseline (*T*_b_), end of treatment (*T*_f_), and follow-up (*T*_fu6_ and *T*_fu12_). Other weight outcome measures, such as variance in weight loss estimations, will be tested. The following formulas will be used to compute these outcomes [40]:

$$ \mathrm{Percentage}\ \mathrm{of}\ \mathrm{total}\ \mathrm{weight}\ \mathrm{regain} = \left(\frac{\mathrm{current}\ \mathrm{weight}-\mathrm{nadir}\ \mathrm{weight}}{\mathrm{weight}\ \mathrm{presurgery} - \mathrm{nadir}\ \mathrm{weight}}\right)\times 100; $$

$$ \mathrm{Percentage}\ \mathrm{of}\ \mathrm{excessive}\ \mathrm{weight}\ \mathrm{regain}=\left(\frac{\mathrm{current}\ \mathrm{weight} - \mathrm{nadir}\ \mathrm{weight}}{\mathrm{excess}\ \mathrm{weight}}\right)\times 100; $$

$$ \mathrm{Percentage}\ \mathrm{of}\ \mathrm{total}\ \mathrm{weight}\ \mathrm{loss}=\left(\frac{\mathrm{weight}\ \mathrm{presurgery} - \mathrm{current}\ \mathrm{weight}}{\mathrm{weight}\ \mathrm{presurgery}}\right)\times 100; $$

$$ \mathrm{Percentage}\ \mathrm{of}\ \mathrm{excessive}\ \mathrm{weight}\ \mathrm{loss}=\left(\frac{\mathrm{weight}\ \mathrm{presurgery} - \mathrm{current}\ \mathrm{weight}}{\mathrm{excess}\ \mathrm{weight}}\right)\times 100; $$

$$ \mathrm{Percentage}\ \mathrm{of}\ \mathrm{alterable}\ \mathrm{weight}\ \mathrm{loss}=\left(\frac{\mathrm{body}\ \mathrm{mass}\ \mathrm{index}\ \mathrm{presurgery} - \mathrm{current}\ \mathrm{body}\ \mathrm{mass}\ \mathrm{index}}{\mathrm{body}\ \mathrm{mass}\ \mathrm{index}\ \mathrm{presurgery} - 13}\right)\times 100\ . $$

Excess weight will be calculated based on metropolitan guidelines [41].

Secondary outcome measures will include behavioral and psychological outcome measures: the number of days engaging in maladaptive eating behaviors (such as grazing, binge eating, or overeating episodes) as well as the number of hours of sedentary and physical activities in the previous month. Psychological symptoms assessed with self-report measures will also be tested. Differences between the intervention group and the control group will be tested at all assessment times. Additionally, midterm secondary outcomes will be tested as predictors of weight outcomes in later assessments.

Baseline (*T*_b_), midterm (*T*_m4_ and *T*_m8_), end of treatment (*T*_f_), and follow-up (*T*_fu6_ and *T*_fu12_) data on primary and secondary outcomes will be compared between the two groups. Repeated measures gathered for the intervention group during the feedback messaging system will be used to study the effect of behavior and psychological outcomes on weight. Repeated assessment enables testing of the course of relevant factors and their relation to weight.

Moderators and nonspecific predictor variables that can affect outcomes without stemming from the intervention are assessed at baseline (*T*_b_); these variables include pre-surgery body mass index, type of surgery, sex, severity of general psychopathology, and frequency of maladaptive behaviors.

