**Methods/design:**

This study is a randomized control trial, which will be conducted in two hospital centers in the North of Portugal; it includes a control group receiving treatment as usual and an intervention group receiving the APOLO-Bari program for one year in addition to treatment as usual. A total of 180 male and female participants who underwent bariatric surgery (gastric sleeve or gastric bypass surgery) for 12 to 20 months will be recruited. Both groups will complete a similar set of questionnaires at baseline, every 4 months until the end of the intervention, and at 6 and 12 months follow-up. Assessment includes anthropometric variables and psychological self-report measures. The primary outcome measure will be weight regain measured at the end of treatment, and at 6 and 12 months follow-up. The secondary aims are to test the cost-effectiveness of the intervention and to investigate psychological predictors and trajectories of weight regain. APOLO-Bari was developed to address the weight regain problem in the bariatric population by offering additional guidance to bariatric patients during the postoperative period. The program includes: (a) a psychoeducational cognitive-behavioral-based self-help manual, (b) a weekly feedback messaging system that sends a feedback statement related to information reported by the participant, and (c) interactive chat sessions scheduled with a trained psychologist in the field.

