## Methods/design

### Design and procedures

This a randomized controlled trial (Current Controlled Trials: ISRCTN37668662), with a superiority design that includes two parallel groups: a treatment-as-usual control group and an intervention group, who receive both treatment as usual and the internet-based program. Consecutive participants will be recruited from two hospital centers in the North of Portugal. Information about the hospital centers involved can be found on the current controlled trials website for our trial registration number.

All participants will be contacted by phone or during their medical appointment and screened for the inclusion and exclusion criteria. Patients meeting these criteria will be invited for an orientation group session to inform them of the program and study procedures. The study will be introduced as a program to support bariatric patients remotely in the long term, which aims to monitor relevant variables and investigate patients’ perception of the utility of these interventions.

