### Proposed sample size and power calculations

The sample size was computed by considering a 0.2 effect size, an alpha level of 0.05, a desired statistical power of 0.8, four predictors or measures and a 20 % dropout rate; this calculation suggested that a total of 180 participants should be recruited (90 in each group).

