### Statistics

Pearson’s chi-square tests will be used to analyze significant differences in the proportion of cases with weight regain and in specific outcome variables between the intervention group and the control group. Significant weight regain will be considered when higher than 5 kg. The Kaplan–Meier approach (together with the log-rank test) will be used to answer the main question of efficacy. Repeated-measures analysis of variance (ANOVA) will be conducted to explore differences between the participant groups for different key variables at various time points. The main effect for surgery type will be investigated. Variables such as log-in frequency, task submission, satisfaction with the program, socio-demographics, pre-intervention scores on self-report measures, and time since surgery will be tested as covariates and predictors of outcomes using Cox regression models. Relevant baseline differences will be included as covariates. Hierarchical linear models will be used to investigate different trajectories of relevant variables assessed from *T*_b_ to *T*_fu12._ Hierarchical linear models are the models that best fit unbalanced designs with unequal number of observations (missing data) per subject. Self-report measures (for depression, impulsiveness, eating disorder and eating patterns, body image, and general distress) will be examined by conducting an analysis of covariance to explore interference with weight outcomes. Post-hoc comparisons will be conducted using Tukey’s procedure. Controlled effect sizes will be calculated using the Cohen’s *d* statistic.

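### Primary weight regain is not fixed to one definition, visit and test, and as defined it does not match the log-rank test named for the main efficacy question

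*Protocol article*

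**What the plan says.** - **Abstract, Methods/design:** "The primary outcome measure will be weight regain measured at the end of treatment, and at 6 and 12 months follow-up". None of the three visits is called decisive.
- **Primary and secondary outcome measures:** "The primary outcome measure will be weight regain assessed at baseline", T_f, T_fu6 and T_fu12. Two regain formulas follow, one dividing by the weight lost from surgery to nadir and one by excess weight. Neither is chosen. Three weight-loss formulas are listed with them.
- **Same section, closing paragraphs:** primary as well as secondary outcomes are to be compared between groups at T_m4 and T_m8 too, which makes five post-baseline visits.
- **Statistics:** the proportion of patients with regain is compared by chi-square, and regain is called significant above 5 kg, with no reference weight. The Kaplan-Meier approach with the "log-rank test) will be used to answer the main question of efficacy", but the event is not defined. Repeated-measures ANOVA is worded as exploratory. Hierarchical linear models are planned for trajectories from T_b to T_fu12.
- **Proposed sample size and power calculations:** the trial is sized by "considering a 0.2 effect size, an alpha level of 0.05, a desired statistical power of 0.8, four predictors or measures" and 20% dropout, giving 180 participants. No event rate or hazard ratio appears.

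**The concern.** A percentage at fixed visits and a time to an event are different endpoints, and a log-rank test cannot analyse the first. The outcome section points to continuous repeated measurements, and the Statistics section points to time to event. The sample size fits the former better: its four measures could be the four visits in the outcome section (T_b, T_f, T_fu6, T_fu12), and it contains nothing a log-rank calculation needs.

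Two things are at stake. If the success criterion can be settled after the data are seen, a positive result cannot be read as confirmatory. And if the threshold test is the real primary analysis, it uses less of the information in a weight that the research team measures at every visit.

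**Working it through.** **Inputs from the protocol article.** Alpha 0.05 (a sample-size input only), power 0.8, effect size 0.2 (metric not stated), four measures, 20% dropout, 180 recruited, 1:1 allocation. Evaluable: 180 × 0.8 = 144, or 72 per group. Sidedness is not stated ("with a superiority design that includes two parallel groups"); two-sided is assumed.

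**1. The plan's own figure.** The inputs do not fix 180.
- Cohen's d = 0.2 for two means: 393 per group, 786 evaluable, 786/0.8 = 983 recruited.
- Cohen's f = 0.2, single comparison: about 198 evaluable, 248 recruited.
- Regression with four predictors and f² = 0.2: 65 evaluable, 82 recruited.
- Repeated-measures ANOVA, group effect, f = 0.2, m = 4 measures with correlation ρ: the single-comparison number is multiplied by (1 + (m−1)ρ)/m. At ρ = 0.60 this is 198 × 0.70 = 138.6, and 138.6/0.8 = 173; the noncentral F calculation gives 175. At ρ = 0.50 it gives 158, and at ρ = 0.65 it gives 185.

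So 180 is compatible with a repeated-measures analysis at an unstated ρ of about 0.60-0.65. This does not prove how it was obtained. The points below do not depend on it.

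**2. What a log-rank test would need.** By Schoenfeld's formula, events = 4(1.96 + 0.84)²/(ln HR)². If 30-37% of 144 patients have an event, there are 43-53 events. Solving for the hazard ratio gives 80% power only at about 0.43-0.46. The 37% is a rate from the Background for regaining more than 25% of lost weight, so it is illustrative here.

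**3. Error rate if several results may count.** For k independent tests it is 1 − 0.95^k. The correlated figures come from simulated null trials of 144 patients with five post-baseline visits. Assumed: correlation 0.5-0.95 between successive visits, correlation 0.80-0.95 between the two formulas, chi-square at the three primary visits, and a cut-off standing in for 5 kg.

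| Results allowed to count | k | Independent | Correlated (simulated) |
|---|---|---|---|
| One log-rank test | 1 | 5% | 4.8-5.4% |
| One formula, three visits | 3 | 14.3% | 7.8-13.1% |
| Two formulas, three visits | 6 | 26.5% | 10.1-20.0% |
| Those plus three chi-squares and log-rank | 10 | 40.1% | 17.0-29.3% |

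T_m4 and T_m8 are not counted as chances of success in these figures.

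**4. Information lost by a threshold.** Splitting one normally distributed measurement at event proportion p keeps φ(z)²/(p(1−p)) of its information: 0.49 at p = 0.20, 0.58 at 0.30 and 0.61 at 0.37. For the log-rank test, take a standardized difference that gives 80% power at one continuous visit: 2.80 × √(2/72) = 0.467. With that difference at the three primary visits, a smaller one before T_f, and visit correlation 0.7-0.9, simulated power was:
- log-rank: 45-59%
- one continuous visit: 78-81%
- mean of the three primary visits: 83-90%

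The log-rank figure is sensitive to when the benefit is assumed to begin. With full benefit already at T_m4 the gap to a single continuous visit narrows considerably; with later benefit it widens.

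**The case against.** The strongest reply is that the Statistics section does choose: it gives the main efficacy question to the log-rank test and words the ANOVA as exploratory. If that test is the only confirmatory one, the 5% rate is kept, and ordering rules can sit in an analysis plan that is not shown. This stands in part. A missing multiplicity rule is not the finding. What remains is that the named test does not fit the outcome called primary and has no stated event, and that the sample size is not built for it. An analysis plan could settle this only by overriding one of the published statements.

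Some stronger readings are tempting but not supported:
- *There is no order among the tests, and all are run at 0.05, so the 5% rate is broken.* One test is singled out, 0.05 appears only in the sample-size paragraph, and no per-test or familywise level is claimed. The inflation is conditional.
- *The log-rank event is regain above 5 kg.* That sentence follows the chi-square test and is not expressly tied to the log-rank.
- *Tukey's procedure is the multiplicity control.* The text says only "Post-hoc comparisons will be conducted using" it; it is not offered as protection for the primary outcome.
- *The retained fraction gives an effective sample size.* It describes one dichotomized visit, not a log-rank test over several visits, and the 37% rate uses another definition of regain.

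It is also fair to say that T_f is not obviously the right single visit, because the objectives stress both short- and long-term efficacy. Defining the log-rank event, reference weight and horizon would also hold 5%.

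**Conclusion.** The concern holds as an internal conflict. Three primary post-baseline visits, two formulas and a third kilogram-based definition are left without a choice, and the test named for the main question cannot analyse the percentages at fixed visits. The error rate is 5% if one fully defined test is the sole basis for a claim. It is about 8-13%, 10-20% or 17-29% if progressively more of the results may count; these ranges rest on assumed correlations and an assumed cut-off. A threshold analysis keeps about 49-61% of the information at one visit for 20-37% events. The simulated log-rank power of 45-59%, against about 80% for one continuous visit, rests also on the assumed effect profile. Whether 180 is enough cannot be judged here, because the effect-size metric is not stated.

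**What to change.** Reconcile the Abstract, the outcome section and the Statistics section by naming one primary variable, one primary visit and one test at two-sided 0.05. For example:

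- **Primary:** percentage of total weight regain at one pre-named visit (T_f, or a follow-up visit if long-term regain is the target). Estimate it as the group contrast at that visit from the hierarchical linear model already planned, adjusted for the T_b value.
- **Next:** test the other two primary visits in a fixed order, each only if the one before it succeeds.
- **Supportive:** the excess-weight formula, the chi-square comparison, the log-rank test with its event and reference weight stated, and the T_m4 and T_m8 comparisons.

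The cost is wording in the registry entry, protocol and analysis plan, and the article reports recruitment as still open. With one named test, 180 need not be raised on account of multiplicity. By contrast, Bonferroni over three visits (0.05/3 = 0.0167) would scale 180 to about 240, and over three visits by two formulas (0.05/6 = 0.0083) to about 278. The downside is that visits later in the order can be claimed only if earlier ones succeed, and the time-to-event result becomes supportive. If the sponsor prefers to keep the log-rank test as primary, its event, reference weight and horizon need defining, and the sample size needs an event rate and hazard ratio.
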